## Objective 4:

Explore whether and how the changes in sanitation service affect the quality of life of the participants included in the study.

### Well-Being Survey

We will collect data on participant well-being through a survey. The team will conduct surveys with a participant representing each of the 50 households enrolled in this study. The surveys will be conducted either in person or by phone at two time points, once before and once after the implementation of the community-wide sanitation system. These surveys will attempt to capture how limited access to sanitation services affects the overall well-being such as distress, fear of legal ramifications, and management related concerns. The surveys will be administered through Qualtrics (https://unc.az1.qualtrics.com/) through a combination of multiple-choice and open-ended questions. If the participant consents, the well-being survey will be recorded and transcribed. The outcome for Objective 4 is an assessment of changes in participants’ quality of life by comparing well-being before and after connection to the wastewater intervention.

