**Analysis::**

We will compare the concentration of culturable *E. coli* in the environment pre- and post-intervention using a time series regression analysis suitable for an interrupted time series. We will couple pathogen measurements with quantitative microbial risk assessment to estimate the potential effect of the intervention on infection risks via key exposure pathways. A linked pre-post survey will focus on self-reported quality of life measures among households connecting to the system.

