We chose to use an ITS instead of a randomized controlled trial because in the context of community-wide infrastructure projects, randomized trials are infeasible and may come with additional equity and ethical concerns, regardless of the fact that health effects specifically attributable to sanitation are variable across trials (25,26). To address concerns that may arise in the absence of a randomized controlled trial, we will include a minimum of 10 additional households from a neighboring community that has existing adequate sanitation and 10 more comparison households with poor sanitation that will not be connected to the intervention until after the conclusion of this study. These 20 comparison sites will allow estimates of (1) background levels of fecal microbes in sample matrices and (2) the influence of non-intervention-related factors (e.g., flooding) on the presence and quantity of sanitation-related microbes. The comparison sites, along with the fact that we are sampling at multiple time points before and after the intervention, will allow us to account for temporal and spatial variation in microbial density.

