### Eligibility and Enrollment

We will recruit households through public presentations at publicized community meetings, through the distribution of postcards via mail, door-to-door contact, and at a booth at the local farmer’s market. Recruitment material will include a description of this project, eligibility requirements, and how participants will be compensated for their time and knowledge. Eligible households will be located in the town or in neighboring, unincorporated communities. All households within the town limits will be eligible to be connected to the intervention. At least one person who is 19 years or older - the age of majority in Alabama - and resides at the enrolled household will act as a participant in the study and answer the survey questions. If the primary participant is unavailable at a given time point, another eligible household member may represent the household for that visit, as long as they meet the study requirements and undergo the informed consent process.

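### Objective 4 surveys all 50 households, but its before/after-connection outcome exists only for the roughly 30 that connect; as stated it is uncontrolled, and the 20 comparison homes have no stated role in it

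*Protocol article*

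**What the plan says.** All of this is in the protocol article.

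- **Objective 4, Well-Being Survey.** Who is surveyed: "The team will conduct surveys with a participant representing each of the 50 households enrolled in this study". When: "once before and once after the implementation of the community-wide sanitation system". What the outcome compares: "comparing well-being before and after connection to the wastewater intervention".
- **Abstract, Analysis.** "A linked pre-post survey will focus on self-reported quality of life measures among households connecting to the system".
- **Interrupted Time Series.** Two comparison groups are added. One is at least 10 homes in a nearby community whose sanitation is already sound. The other is described as "10 more comparison households with poor sanitation that will not be connected to the intervention until after the conclusion of this study". The uses given for these sites, here and again under Limitations, are background microbial levels and the effect of outside factors such as flooding on microbes. Well-being is not mentioned.
- **Methods and analysis.** The well-being survey is given at time points three and six only.
- **Eligibility and Enrollment.** If the primary participant is unavailable, "another eligible household member may represent the household for that visit".
- **Limitations.** The text accepts that concurrent trends could be credited to the intervention. Under Bias it expects social desirability bias and sees a chance of courtesy bias.

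**The concern.** The places that describe the well-being outcome do not agree on whose change is measured or from what event. The survey covers everyone enrolled and is timed around implementation of the community system. The outcome is timed around a household's own connection. A comparison home can be surveyed before and after implementation, but never before and after its own connection within the study.

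The reading that fits the outcome sentence and the abstract is a before/after change in the connecting homes. That has a weakness of its own. The soil *E. coli* analysis has three time points on each side and so can project a prior trend. The well-being outcome has one survey on each side and cannot. Any general change over the period, and any drift in how people answer, goes into the estimate. The mitigation offered for reporting bias, pairing survey answers with environmental data, does not correct a well-being score.

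Meanwhile 10 homes with poor sanitation and no connection answer the same survey, and no use of their answers is stated. The rule allowing a substitute respondent adds a smaller problem. It does no harm to soil sampling, but for a change in a participant's own quality of life it can turn a difference between two people into an apparent change in one.

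**Working it through.** **1. How many homes connect.** The Sample Size Calculations reproduce as printed, with two-sided 5% significance and 80% power:

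- Equation 1: m = 2 × (1.96 + 0.84)² × 5.2 × (1 − 0.16) / (6 × 4.3 × 0.45²) = 13.1 (stated: 13).
- Equation 2: n = 13 × (1 + 0.17) × (3 − 1) = 30.4 (stated: about 30).
- 30 + 10 + 10 = 50, the enrolled total.

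So about 30 homes can supply a before/after-connection change, and 20/50 = 40% cannot. These calculations concern soil *E. coli*. No effect size, standard deviation, test or power is given for well-being.

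**2. What pooling would do, if it were done.** Let the mean change in connecting homes be Δ and that in comparison homes be fΔ. The mean over all 50 is (30Δ + 20fΔ)/50 = (0.6 + 0.4f)Δ.

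| f | Pooled mean / Δ | Attenuation |
|---|---|---|
| 0 | 0.60 | 40% |
| 0.25 | 0.70 | 30% |
| 0.50 | 0.80 | 20% |
| 1 | 1.00 | 0% |

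The document does not give f. Restricted to connecting homes, there is no attenuation from this source.

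**3. What a concurrent comparison would cost in precision.** Assume the same variance s² of the within-home change in both groups.

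- Connecting homes alone: SE = s√(1/30) = 0.183s.
- Difference in differences against the 10 unconnected poor-sanitation homes: SE = s√(1/30 + 1/10) = 0.365s.
- Ratio: 0.365/0.183 = 2.0.

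**4. What it would remove.** Suppose the change in connecting homes is effect + shared drift + bias from having received a system, and the change in unconnected homes is shared drift. The difference leaves effect + bias from having received a system. Drift common to both groups goes; courtesy toward the new system stays.

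**The case against.** The best defence is that the protocol is coherent when its parts are read together. Surveying all 50 is data collection; the demographic and sanitary surveys also go to all 50. The outcome sentence can apply only to homes that connect, and the abstract names that group. Much of this stands. A reader might infer that the change will be averaged over all 50 and is therefore diluted by 40%. No sentence says so, and the 40% also needs exactly zero change in the comparison homes.

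A reader might also infer a loss of power, for example from 80% to Φ(2.802 × 0.6 × √(50/30) − 1.96) = 58%. That borrows the 80% set for soil *E. coli*. Objective 4 is secondary, is framed as exploration, uses partly open-ended questions and states no test, so no power figure can be attached to it.

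Nor can one say that the comparison homes are barred from serving as controls. The article is silent on this, surveying them is compatible with that use, and modelling detail may sit in a fuller document. The biases are openly disclosed. Substitution is the exception, since there is a primary participant and the survey can be done by phone.

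The objection also bites on the remedy. On the same borrowed benchmark, a difference in differences with twice the standard error would have Φ(2.802/2 − 1.96) = about 29% power. It therefore cannot replace the within-home change.

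What the objection does not answer is that the contrast, as worded, has no concurrent comparison, while the data for one are being collected and the stated uses of those homes are microbial.

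**Conclusion.** The point holds in a limited form. The article should state one analysis population for Objective 4. As worded, the outcome is an uncontrolled before/after comparison of self-report in about 30 homes. It is open to secular change and to response bias that the article itself anticipates, and the 20 comparison homes have no stated part in it. Attenuation of up to 40% is a conditional worst case, not a property of the plan.

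This rests on all non-comparison homes connecting (50 − 20 = 30) and, for the precision figure, on equal variances of change in the two groups. The difference in differences also assumes that connecting and unconnected poor-sanitation homes would otherwise have changed alike. Because Objective 4 is secondary and exploratory, this is a worthwhile improvement and does not threaten the primary outcome.

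**What to change.** 1. In the Well-Being Survey section, state that the before/after change is estimated in households that connect, in agreement with the abstract, and use one anchor for both the survey timing and the outcome.
2. Alongside that change, report a difference in differences against the 10 unconnected poor-sanitation homes over the same period. The comparison homes have no connection date, so say how their two surveys are matched in time. Show the adequate-sanitation homes separately.
3. Keep the same respondent at time points three and six where possible, record any substitution, and repeat the analysis without changed-respondent pairs.

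**Cost.** These are mainly wording changes and need no extra visits, since the surveys are already planned in all 50 homes. The difference in differences has about twice the standard error of the connecting-home change, so it should be a supplement with its interval shown. It will not remove courtesy bias specific to having received a system, and the report should say so. Dropping changed-respondent pairs reduces the number of homes in that repeat analysis.

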## Limitations:

### Secular trends in exposures or outcomes

Because ITS analyses compare pre- and post-intervention trends of outcome measures, a limitation of this approach is the existence of non-intervention, secular changes that obscure or complicate the attribution of effects to the point of intervention. Additionally, an ITS does not include a control group; therefore, simultaneous trends may be incorrectly attributed to the intervention itself. Weather-related events, such as rainfall and temperature, are examples of independent variables that could act as potential confounders because extreme rainfall or temperatures can increase blockages and breakages in onsite wastewater treatment systems (37). We will closely monitor rainfall and adjust our analyses to account for any differences observed by incorporating comparison sites. However, it is important to note that the potential for residual confounding cannot be eliminated completely in this study design. As previously described, we plan to include a minimum of 10 comparison sites with existing adequate sanitation and 10 comparison sites with poor sanitation that will not be connected to the intervention until after this study concludes. This plan will allow estimates of (1) background levels of fecal microbes in sample matrices and (2) the influence of non-intervention-related factors (e.g., flooding) on the presence and quantity of sanitation-related microbes.

### Bias

There are several possible sources of bias in this study design. We are specifying microbial targets *a priori*, limiting analysis of samples to a pre-selected list of fecal indicators and enteric pathogens. We are attempting to minimize this bias by basing our TAC design on baseline data from a series of studies before the impact assessment. Another form of possible bias is reporting bias in the surveys and interviews. To attempt to minimize reporting bias, we are pairing this data with the independent quantitative environmental sample data collected.

Additionally, there is potential for volunteer or self-selection bias, as participation in this study is not required for households connecting to the system. This may bias data by only including people who would typically volunteer to be a part of a study and/or those who have enough time to participate in research activities. Similarly, participants must be willing to pay a monthly maintenance fee to connect to the intervention (at the time of this writing, the exact pricing for tariffs or connection fees have not been established), which could select for more affluent participants while excluding those unable to afford the fee. It is also possible that households with the most inadequate or failing sanitation systems may be more motivated to participate, seeing greater potential benefit from the intervention. Furthermore, there is a chance that we will experience courtesy bias, which occurs when participants give overly positive responses in surveys or interviews to avoid offending the researcher or to present themselves favorably. We will attempt to minimize the amount of courtesy bias in this study by working with the community advisory group, being very clear on how this data will be used, and making sure it is known that this team is working for the community and is not affiliated with nor invested in the intervention itself. Finally, we predict that we will also experience social desirability bias, which is when participants respond to certain questions in a way that they believe will positively portray them in line with social norms. We will attempt to minimize the amount of social desirability bias in this study by ensuring participants that their responses will be kept completely confidential and anonymous.

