Without reliable and affordable alternatives, many households use what is known locally as “straight piping.” Straight-piping consists of a pipe that transports untreated wastewater (black water and/or gray water) directly from the home to an uncontained pit, ditch, stream, waste field, or another “disposal area” where it is accessible to people and animals (16). The Alabama Center for Rural Enterprise claims that most straight pipes are less than 10 meters long, suggesting that discharge points are typically within close proximity to homes (15). It is difficult to find data that encapsulates the full scope of this issue since homeowners can face legal repercussions for discharging wastewater via straight pipes. The use of “inadequate sewage disposal systems” is a criminal misdemeanor in Alabama that could result in fines – as much as $500 for each citation – eviction, and – in some cases – arrest (7). Considering the barriers to municipal sewerage and failures of onsite sewage disposal systems and the gaps these create, there is a need for innovation in this space to identify technologies and infrastructure models suitable for rural regions such as the Black Belt.

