### Demographic Survey

The team will conduct a demographic survey in person during the first household visit for sampling. The demographic survey will be self-administered by a participant at each of the 50 households unless the participant specifies otherwise. This survey is intended to gather information about the characteristics of the enrolled participant and the household as well as contact information for future sampling and surveys. Each survey will be administered through Qualtrics (https://unc.az1.qualtrics.com/) and will include multiple-choice and open-ended questions. Questions will include but not be limited to the participant’s gender and race/ethnicity, household income range, and preferred method of future contact.

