### Sanitary Inspection Survey

The team will conduct observational and participant-taken sanitary inspection surveys in person or over the phone pre- and post-intervention. The observational survey will be conducted at all 50 households by the enumerator and is intended to elucidate current management practices for wastewater at the home as well as to document any visual damages to existing infrastructure. The written participant sanitation surveys will be self-administered by a participant at each of the 50 households unless the participant notes otherwise and are intended to gather information about each household’s water and sanitation practices. Each survey will be administered through Qualtrics (https://unc.az1.qualtrics.com/) and will include multiple-choice questions, open-ended questions, and photographs of current infrastructure. Questions will include where gray and black water is discharged, damage to infrastructure, and what type of water is used for drinking and hygiene.

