## Data Availability

Upon publication of results for this study, the household data will be fully deidentified and made freely available in a permanent online repository (https://osf.io/9kvfa/).

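### Participants are to be assured that their answers are anonymous, but the study's own procedures make them confidential and coded at most

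*Protocol article*

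**What the plan says.** Under Limitations, the Bias section predicts social desirability bias in the surveys. The one measure it names against that bias is "ensuring participants that their responses will be kept completely confidential and anonymous".

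Other sections describe how the answers are gathered and kept:

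- The Demographic Survey section says the first survey collects characteristics of the participant and household "as well as contact information for future sampling and surveys". Its listed items include "the participant’s gender and race/ethnicity, household income range, and preferred method of future contact".
- The abstract's Analysis paragraph says: "A linked pre-post survey will focus on self-reported quality of life measures among households connecting to the system".
- The Sanitary Inspection Survey section covers wastewater discharge and damage to infrastructure, using multiple-choice items, "open-ended questions, and photographs of current infrastructure".
- The Well-Being Survey section says: "If the participant consents, the well-being survey will be recorded and transcribed".
- The Ethics and dissemination section says identifiable data are kept apart on protected servers, and that a household can have a summary of its own site results on request.
- The Data Availability section says "the household data will be fully deidentified and made freely available in a permanent online repository".

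On what is at stake, the Background says use of an inadequate disposal system "is a criminal misdemeanor in Alabama that could result in fines" of up to $500 per citation, with eviction and in some cases arrest also possible.

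**The concern.** Anonymous and confidential are different promises. Anonymous means that nobody, including the study team, can connect an answer to the person who gave it. Confidential means that the team can make the connection but undertakes not to disclose it. Participants here are asked where their household's wastewater goes and whether they worry about legal consequences. They decide what to reveal partly on the strength of the assurance. If it overstates the protection, they are misinformed on a point that bears on their legal position.

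The same assurance is also the only control named for a bias that the authors expect to occur. A control should be one that the design can deliver.

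**Working it through.** No figure in the plan is at issue, so the main check sets the assurance against each procedure.

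**Can the answers be anonymous to the team?**

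1. *Contact details.* The demographic survey is done in person at the first household visit and itself collects contact information. Those answers arrive together with a direct identifier.
2. *Linkage.* The before and after surveys are linked. Linkage alone could work through a code that participants hold. Here, however, the same household is visited at six time points and its soil is resampled at fixed locations, so the code must map to a known address.
3. *Recording.* If the participant agrees, the well-being survey is recorded. A voice recording is not anonymous. This applies only to those who consent to it.
4. *Return of results.* Giving a household its own site summary requires a key from the data to the home.
5. *Storage.* Keeping identifiable data apart from other data presupposes that such data exist. It is a confidentiality measure.

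Items 1, 4 and 5 are each enough to show that the team can identify households. Items 2 and 3 reinforce this. The confidential half of the assurance agrees with the Ethics section; the anonymous half agrees with none of these sections.

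**How far can disclosure risk from the open deposit be sized?**

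The documents give about 140 households offered connection (Description of Intervention) and 50 enrolled (Objective 1). They do not give the variables to be released. Any number C of distinct profiles in the released file is therefore an assumption. If households were spread evenly over C profiles, the expected share with a unique profile among N households is (1 − 1/C)^(N − 1).

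| Assumed C | Unique among the 50 enrolled, (1 − 1/C)^49 | Unique among 140, (1 − 1/C)^139 |
|---|---|---|
| 6 | about 0% | about 0% |
| 24 | 12% | 0.3% |
| 36 | 25% | 2% |
| 90 | 58% | 21% |
| 120 | 66% | 31% |

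With profile frequencies proportional to 1/rank instead of even, C = 24 gives 14% and 3%, and C = 90 gives 35% and 18%. The first results column is relevant to someone who already knows which homes took part, the second to someone who does not. Using 140 as the pool is itself approximate, because the 10 adequate-sanitation comparison homes are in a neighboring community. The range runs from negligible to substantial, and it depends on a release list that the article does not give.

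**The case against.** The strongest reply is that this is one loosely chosen word. The article plainly intends confidentiality: identifiers are stored separately, results are shared in deidentified form, and consent covers risks, confidentiality protections and how results will be shared. The consent text is not shown, so what participants are actually told cannot be judged. The effect on the data is also limited. The primary outcome is culturable *E. coli* in soil. Objective 2 has an enumerator's inspection at all 50 households, and the Bias section pairs survey answers with environmental measurements. Objective 4 depends most on candor, and nothing in the documents shows that participants would under-report because of the wording.

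Most of this stands. It limits the consequence but does not make the assurance accurate. The Bias section says what participants will be assured of, and no fuller protocol or data management plan could make answers tied to contact details anonymous.

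A reader might go further and infer that participants can be re-identified from the open repository as users of an unlawful discharge. The documents do not support that. The Data Availability section says the household data will be fully deidentified first. The survey sections list what is collected, and no section says that demographics, photographs, transcripts or connection dates will be posted. The deidentification method is something an article may leave to a data management plan. Deposit follows publication of results, after the Phase II connections, so connected homes should by then have had their old systems replaced. The 10 poor-sanitation comparison homes, which stay unconnected until the study ends, are the ones for whom the question remains most open.

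**Conclusion.** The concern holds for the assurance. The word *anonymous* in the Bias section contradicts the document's own procedures and should be corrected, because the answers concern conduct that the Background describes as criminal. This conclusion rests on the text alone and needs no assumption about what is released.

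The size is that of a wording error with an ethical consequence. No statistical result changes: the primary analysis, the sample size and the count of 50 households are untouched. Any effect on Objectives 2 and 4 through less candid answers is possible but cannot be quantified from the documents. Disclosure through the deposit is likewise a possibility in a pool of about 140 households. The shares tabulated above are illustrations on assumed profile counts and are not findings about this dataset.

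**What to change.** In the Bias section, replace the reference to anonymity with wording such as *confidential, with identifiers stored separately under a link key*. Use the same wording in participant scripts, and reconcile the Bias section with the Demographic Survey, Well-Being Survey, Ethics and dissemination, and Data Availability sections. The study began in August 2024, so the team should check what participants already enrolled were told and give the corrected statement to anyone who was promised anonymity.

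When the commitment to full deidentification is put into practice, consider how combinations of sanitation type, demographics and dates could single out a home in so small a community. How to balance that against the stated open-science commitment is the investigators' choice; controlled access or a minimum cell size are options and are not required by this point.

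The cost is a phrase in the article and scripts, plus a short notice to earlier participants if needed. The accurate promise is slightly weaker, so a few participants may answer more guardedly.
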